## Secondary Outcome Measures

### Clinician Rated Measures:

**Global improvement** will be assessed by a blinded assessor using CGI- Improvement (CGI-I).^19^ The CGI-I is a single-item measure that rates overall symptom change compared to baseline on a 7-point scale, where lower scores indicate greater improvement.

**Global and impaired functioning** will be assessed using the clinician-rated Children’s Global Assessment Scale (CGAS).^20^ The CGAS is a single-item measure ranging from 1 to 100, with higher scores indicating better overall functioning.

**Functional impairment** across five domains: school, everyday activities, friendships and social life, recreation and hobbies, and family or close relationships will be measured using The Work and Social Adjustment Scale (WSAS)^21^will be used to assess. The scale consists of five items, yielding a total score ranging from 0 to 40, with higher scores indicating greater impairment.

**Symptoms of depression and anxiety** will be assessed using The Revised Child Anxiety and Depression Scale (RCADS-47).^22^ RCADS-47 measures symptoms of both anxiety and depression, yielding a total score ranging from 0 to 141, with higher scores indicating greater symptom severity.

**Clinician predictions** of treatment response will be collected prior to randomization. Clinicians will be asked to make an overall assessment based on all available information about the participant and estimate the most likely outcome on the CGI-S/I at the end of treatment.

**Therapist time:** The total therapist time spent on both reading what adolescents and parents have written in the modules and providing feedback and messaging participants will be calculated.

**Patient adherence** will be assessed by a clinician midway through treatment using Internet Cognitive Behavior Therapy Adherence Scale (PIAS).^23^

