### Primary Outcome Analysis

To evaluate the primary outcome, change in CGI-S scores will be analyzed using a cumulative link mixed model (CLMM) implemented in the ordinal package in R (R Project for Statistical Computing).^42^ The model will include a random intercept for participant, a dummy-coded site variable, a dummy-coded time variable (before treatment, immediately after treatment, and 3 months after treatment, with before treatment as the reference category), the treatment condition, and the interaction between the time variable and treatment. Coefficients from the CLMM represent the log odds of being classified in a higher CGI-S category, these will be converted to odds ratios.

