### Secondary Outcomes Analyses

For secondary outcomes, linear mixed-effects regression models, with the same predictors and covariates as the CLMM model will be used. Effect sizes will be estimated as Cohen d for mixed-effects models by dividing the unstandardized β coefficient for the time x treatment interaction by the baseline SD, with 95% bootstrap confidence intervals derived from 1000 simulations. Under the assumption that data are missing at random, mixed-effects regression analyses for repeated measures (including all assessment points), provide unbiased estimates and standard errors.^43^ This assumption indicates that, conditional on observed data, the probability of missingness depends only on observed variables and not on unobserved values.^44^ If >30% of the primary outcome data are missing at the primary end-point, we will conduct NMAR sensitivity analyses to assess the robustness of the results to departures from the MAR assumption. For CGI-I, the number of participants classified as responders will be presented. Treatment response is defined as a CGI-I rating of 1 (“very much improved”) or 2 (“much improved”).^15,45,46^ Differences between treatment groups in participant satisfaction and therapist time will be analyzed using independent samples t tests. To examine whether blinded assessors’ guesses of treatment allocation differ from chance, a t test will be conducted. All tests will be 2-sided, with statistical significance set at P < .05.

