### Health economic evaluation

The analysis will adhere to the Consolidated Health Economic Evaluation reporting Standards 2022 (CHEERS 2022) statement. The following analysis will be conducted: a cost-utility analysis using cost per quality-adjusted life year (QALY) gained; and a cost-effectiveness analysis using cost per responder.^47,48^ Based on previous research,^15,45,46^ treatment response will be defined as a CGI-I rating of 1 (“very much improved”) or 2 (“much improved”). QALYs will be estimated using CHU9D utility scores, which will be derived using a validated algorithm.^49^; and total QALYs over the trial period will be calculated using the area under the curve approach.^50^ Analyses will be conducted from both a health care sector and a societal perspective. Total costs will include the costs of administering POET or supportive treatment, as well as the use of other societal resources collected with the TIC-P, including health care resources, medication, social and school support services, and productivity losses due to absenteeism and presenteeism related to work. Total costs will be calculated for the full trial period by multiplying frequencies of resources by their respective unit costs. Regression models will be employed to estimate the differences in mean costs and mean effects between the groups over time. Incremental cost-effectiveness ratios (ICER) will be calculated as the difference in costs between the two interventions divided by the difference in effects (QALYs and response), for each type of analysis and each costing perspective. Sensitivity and scenario analysis will be conducted to explore the uncertainty around the estimates and different assumptions. The uncertainty will be plotted on cost effectiveness planes, and the probability of the intervention being cost effective will be calculated across different value levels a decision maker would be willing to pay and plotted on cost effectiveness acceptability curves.^51^

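### The clinical analysis fixes CGI-I response as a bare count with no between-arm estimate, while the health economic analysis plans a between-arm difference in the same response

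*Protocol*

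**What the plan says.** The protocol lists CGI-I under Secondary Outcome Measures, Clinician Rated Measures, and describes it so: "The CGI-I is a single-item measure that rates overall symptom change compared to baseline on a 7-point scale". Table 2 schedules it immediately after treatment and at 3, 12 and 60 months, and leaves the baseline cell empty, as it must for a change rating.

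Three statements in Secondary Outcomes Analyses bear on it.

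- The general rule: "For secondary outcomes, linear mixed-effects regression models, with the same predictors and covariates as the CLMM model will be used". Under Primary Outcome Analysis, that model's time variable is dummy-coded "with before treatment as the reference category". The effect size is the time-by-treatment coefficient divided by the baseline SD.
- The specific rule: "For CGI-I, the number of participants classified as responders will be presented". A responder is a participant rated 1 or 2.
- The rule for two other measures: "Differences between treatment groups in participant satisfaction and therapist time will be analyzed using independent samples t tests".

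Health economic evaluation uses the same responder definition in "a cost-effectiveness analysis using cost per responder". It plans regression models for the between-group difference in mean effects, and a ratio whose denominator is the difference in QALYs or in response.

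**The concern.** The clinical section gives a blinded clinical outcome less analysis than therapist time or satisfaction, each of which gets a formal comparison of the arms. Two responder counts are not an effect estimate: they carry no interval and no adjustment for site or baseline severity. This is a method that the protocol states, so it is not a detail left open for a statistical analysis plan.

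Two consequences follow. The clinical report would show responder numbers that invite comparison without the means to make it. The economic report would contain a between-arm difference in the same responder variable, from a model that the clinical section does not mention. The trial could then publish two accounts of response that need not agree. Long-term and distal outcomes data extends the same methods to 1 and 5 years, so on its face the count-only approach carries forward.

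**Working it through.** **Does the general rule cover CGI-I?** Set the sections side by side.

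1. The shared model needs a value at the reference visit, before treatment.
2. CGI-I has none (Table 2), because it rates change from that visit.
3. The time-by-treatment contrasts against baseline therefore cannot be formed, and there is no baseline SD to divide by.
4. The specific rule replaces the model with a number of responders. On either reading, the clinical section yields no usable between-arm estimate for CGI-I.

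**Does the economic section cover it?** Yes, for its own purpose. It plans regression for differences in mean effects and divides by the difference in response. The mismatch is between the two sections; it is not an absence throughout the protocol.

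**The plan's own figures.** The protocol gives no rate, difference or power for CGI-I response. The figures that can be checked are consistent:

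- Sample size: 350 / 0.9 = 388.9 against the stated 388 (388 × 0.9 = 349.2).
- Rated per arm: 194 × 0.9 = 174.6. A two-sample comparison at d = 0.30 with that number has power 0.800 on the post-treatment score and 0.899 with baseline adjustment at a correlation of 0.5. This agrees with the stated power of over 80%.

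**Uncertainty that the counts leave unreported.** Assume 50% response in both arms and 175 rated per arm:

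- half-width = 1.96 × √(2 × 0.25 / 175) = 0.105, or about 10.5 percentage points.

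**Is an estimate worth having at this sample size?** The control response rates below are assumptions. The odds ratio of 2.2 is borrowed from the primary power analysis, where it refers to the CGI-S interaction, so this is illustration only. POET rate = o / (1 + o), with o = 2.2 × p₀ / (1 − p₀). Half-width = 1.96 × √{[p₀(1 − p₀) + p₁(1 − p₁)] / 174.6}.

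| Control p₀ | POET p₁ | 95% half-width | Two-sided power |
|---|---|---|---|
| 20% | 35.5% | 9.3 points | 0.90 |
| 30% | 48.5% | 10.1 points | 0.95 |
| 40% | 59.5% | 10.3 points | 0.96 |

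A between-arm estimate of response is therefore feasible with the planned enrolment.

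**The case against.** The strongest defence is that a descriptive count is a legitimate choice. Hypothesis 1.1 names global symptom severity, symptoms and functioning. Global severity is tested on CGI-S, the primary outcome, immediately after treatment and at 3 months. Reporting a dichotomised companion rating descriptively avoids another test without multiplicity control, and if the number rated is printed beside each count, a reader can work out a crude difference and interval. Part of this stands: no primary conclusion depends on CGI-I. It does not explain why satisfaction and therapist time are compared formally and CGI-I is not, or why the protocol needs a response difference in one section and supplies none in the other. A crude hand calculation also lacks the site and baseline-severity adjustment.

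A reader might infer three stronger things, and the protocol supports none of them.

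- *That the cost-per-responder ratio has no between-arm estimate.* Health economic evaluation plans one, together with sensitivity analyses, cost-effectiveness planes and acceptability curves.
- *That missing ratings necessarily distort the counts.* Take 50% response in both arms, with 5% against 15% unrated. The counts are 194 × 0.95 × 0.5 = 92 and 194 × 0.85 × 0.5 = 82, about 5 points apart out of 194. Divided by the numbers rated (184 and 165), both arms show 50%. The gap needs unequal missingness and a denominator of all randomised; the protocol states neither. If missingness depended on response, the number-rated denominator would not be a full remedy either, but nothing in the protocol indicates that. The denominator for a descriptive count is ordinary analysis-plan content.
- *That CGI-I alone departs from a missing-at-random approach.* The two outcomes given t tests also fall outside the mixed models for which that argument is made.

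**Conclusion.** The point holds in limited form. The clinical analysis fixes CGI-I response as a number of responders with no effect estimate or interval, the shared baseline-referenced model cannot be applied to CGI-I, and the economic section plans a response difference that the clinical section does not provide.

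The unreported uncertainty is about ±10.5 points at 175 rated per arm and 50% response, or 9 to 10 points across the other assumed rates. These figures rest on about 10% attrition, equal in the arms, and on assumed response rates, since the protocol gives none. The matter is worth correcting because the better method is cheap. It does not touch the primary endpoint, the sample size or the validity of the economic analysis.

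**What to change.** In Secondary Outcomes Analyses, replace the count-only sentence with a stated model. Analyse CGI-I response (1–2 against 3–7) immediately after treatment and at 3 months by logistic mixed regression with arm, visit, arm-by-visit, site (Region) and baseline CGI-S as terms, and a random intercept for participant. At each visit, report the odds ratio and the standardised risk difference with 95% confidence intervals. Keep the responder counts as description, with the number rated in each arm as denominator. State in Health economic evaluation that the cost-per-responder ratio uses this same response estimate.

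The cost is one additional model on data already being collected, with no change to visits or conduct. The downside is one more secondary estimate, which should be labelled as secondary and without multiplicity control.

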# Methods: Patient and public involvement, trial design

## Overall trial design

This study adopts a RCT design. The study has an active control treatment. The study will be hosted at different well-established youth primary care services in Sweden. Participants are assessed before treatment and then weekly during treatment. Subsequently, follow-up assessments are completed; immediately after treatment, 3 months after treatment, 1-year, 5-year and 10-year after treatment. 388 adolescents (ages 12-17 years) with mild- moderate mental health problems will be randomized to one of two treatment conditions:

a) Online emotion regulation treatment (n = 194)

b) Online supportive treatment (n = 194).

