# Methods: Assignment of interventions

## Randomization

Eligible participants will be randomly assigned (1:1) to either the POET intervention or the Supportive Treatment condition. Randomization will be conducted in blocks of four or six within each participating Region. An independent researcher, not involved in participant recruitment or treatment delivery, will perform the randomization using an online system (Sealed Envelope Ltd) that employs a secure pseudo-random number generator.

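### The t tests for satisfaction and therapist time leave out Region, the factor within which randomisation is blocked, so their intervals are somewhat too wide if Regions differ

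*Protocol*

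**What the plan says.** Protocol, Randomization: "Eligible participants will be randomly assigned (1:1) to either the POET intervention or the Supportive Treatment condition", and "Randomization will be conducted in blocks of four or six within each participating Region". Region is therefore the randomisation stratum.

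Protocol, Primary Outcome Analysis: the cumulative link mixed model for CGI-S carries "a dummy-coded site variable" alongside time, treatment and their interaction. Protocol, Secondary Outcomes Analyses: for the secondary outcomes, "linear mixed-effects regression models, with the same predictors and covariates as the CLMM model will be used". These models therefore all have a centre term.

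The same section treats two measures differently: "Differences between treatment groups in participant satisfaction and therapist time will be analyzed using independent samples t tests". It adds neither Region nor site to these tests. The significance rule covers them too: "All tests will be 2-sided, with statistical significance set at P < .05".

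The protocol does not define site or say how it relates to Region. Overall trial design says only this about the hosts: "The study will be hosted at different well-established youth primary care services in Sweden".

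**The concern.** An independent-samples t test treats the arms as two unrestricted random samples. Here they are not: blocking keeps the arms nearly equal in size within every Region, so a Region with high satisfaction, or with long therapist time, contributes about equally to both arms. That part of the variation largely cancels from the difference in means. The t test does not know this and keeps it in the pooled variance. The standard error is then too large, the interval too wide, and the test more conservative than its stated level.

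What is at stake is precision. Therapist time matters most, because the section on the active control treatment says the control is meant to account for therapist attention, and therapist time bears directly on whether attention was similar in the two arms. The protocol does not say how a non-significant difference would be read, but if it were taken as support for matched attention, an over-conservative test would lean towards that reading.

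**Working it through.** **Inputs from the protocol**
- 388 participants, 194 per arm, 10% attrition, ICC 0.5, two-sided α = .05, and more than 80% power at d = 0.30 (Power analysis, Secondary continuous outcomes).
- Blocks of four or six within Region, 1:1 (Randomization).

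**Assumed, because the protocol does not give them**
- The share *s* of outcome variance lying between Regions: 5%, 10% and 20%.
- The number of Regions, needed only for the simulation: 4 or 8.

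**Step 1. The plan's own figure.** Analysable per arm: 194 × 0.9 = 174.6. With ICC 0.5, the SD of a change score in baseline-SD units is √(2(1 − 0.5)) = 1. SE = √(2/174.6) = 0.107. Power = Φ(0.30/0.107 − 1.96) = Φ(0.843) = 80.0%, which agrees with the stated figure. A post-treatment comparison with SD 1 has the same SE, so the same benchmark serves for satisfaction and therapist time.

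**Step 2. Effect of leaving Region out.** Set the total variance to 1 and take the arms as balanced within Region.
- True SE of the difference = √(1 − s) × √(2/n).
- SE used by the t test ≈ √(2/n).
- Ratio r = 1/√(1 − s).
- Actual type I error = 2(1 − Φ(1.96 r)).
- Power of the t test = Φ(0.30/true SE − 1.96 r); with Region in the model = Φ(0.30/true SE − 1.96).

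For s = 0.10: r = 1/√0.90 = 1.054; 1.96 × 1.054 = 2.066; type I error = .039. True SE = 0.949 × 0.107 = 0.1015, and 0.30/0.1015 = 2.955. Power is Φ(2.955 − 2.066) = 81.3% for the t test and Φ(2.955 − 1.96) = 84.0% with Region.

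| Assumed Region share | SE too large by | Actual type I error | Power, t test | Power, Region in model |
|---|---|---|---|---|
| 5% | 2.6% | .044 | 80.6% | 82.0% |
| 10% | 5.4% | .039 | 81.3% | 84.0% |
| 20% | 11.8% | .028 | 82.7% | 88.0% |

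**Step 3. Simulation.** The formulas assume exact balance within Region, whereas incomplete last blocks and dropout disturb it a little. Trials of 388 participants were simulated with blocks of four or six within Region and 10% random loss, 4,000 per setting.

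| Region share | Type I error, t test (4 / 8 Regions) | Type I error, Region dummies (4 / 8 Regions) |
|---|---|---|
| 5% | .043 / .043 | .046 / .048 |
| 10% | .041 / .037 | .051 / .047 |
| 20% | .034 / .028 | .051 / .048 |

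The simulation error at a true rate of .05 is √(.05 × .95/4000) ≈ .003. The direction and rough size of the formulas are confirmed.

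**Step 4. Would site dummies do instead?** With three sites nested in each Region, a linear model of the outcome on treatment and site dummies kept type I error between .046 and .056 over all settings, including shares of 0 and 2%. The extra parameters cost a little power: with 8 Regions and a 10% share, 81.2% against 83.5% with Region dummies. A site term nested in Region therefore absorbs the stratum.

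**The case against.** The strongest reply is that this is harmless. With 1:1 blocking the estimate is essentially unbiased and the error can only be conservative, so no false positive claim follows. Neither measure is named in the research questions and hypotheses. The same therapists deliver both arms through a common online format, so Regions may differ little, and at a 5% share the standard error is only 2.6% too large. At d = 0.30 the unadjusted test still passes 80% power by the formula at every share considered. All of this stands. It makes the point small but does not remove it: the protocol names the test, drops the centre term that its other models carry, and gives no reason.

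A reader might also infer that the mixed models are misadjusted because they use site while randomisation uses Region. The documents do not support that. It would need a site that is coarser than Region or cuts across Regions, and the protocol nowhere says so; national recruitment and online delivery make it conceivable, no more. If site means Region, or a service within one, its dummies already absorb the stratum. Replacing site by Region could even remove a finer adjustment.

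**Conclusion.** The point holds for two comparisons only, satisfaction and therapist time. Their intervals are too wide and their tests conservative to the extent that Regions differ: by 2.6% to 11.8% in standard error over assumed shares of 5% to 20%, with a loss of about 1.4 to 5.3 percentage points of power at d = 0.30 (82.0 − 80.6 and 88.0 − 82.7). If Regions do not differ, nothing is lost. The size rests wholly on a variance share that the protocol does not give, and on near-balance of the arms within Region. The point estimates stand. No effect on the primary analysis or the other mixed-model analyses has been shown. This is a minor, nearly free improvement, not an error that threatens a conclusion.

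**What to change.** In Secondary Outcomes Analyses, replace the two independent-samples t tests with a linear regression of CSQ score, and another of therapist time, on treatment plus dummy variables for the Region used at randomisation. Site may serve instead if every site lies within one Region. Report the adjusted mean difference with its 95% confidence interval. Keep the site term in Primary Outcome Analysis as it is; one sentence on how site relates to Region would remove the ambiguity.

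The cost is a change of wording and a few degrees of freedom. Region has to be known to allocate a participant, so no new data are needed.

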### Health economic evaluation

The analysis will adhere to the Consolidated Health Economic Evaluation reporting Standards 2022 (CHEERS 2022) statement. The following analysis will be conducted: a cost-utility analysis using cost per quality-adjusted life year (QALY) gained; and a cost-effectiveness analysis using cost per responder.^47,48^ Based on previous research,^15,45,46^ treatment response will be defined as a CGI-I rating of 1 (“very much improved”) or 2 (“much improved”). QALYs will be estimated using CHU9D utility scores, which will be derived using a validated algorithm.^49^; and total QALYs over the trial period will be calculated using the area under the curve approach.^50^ Analyses will be conducted from both a health care sector and a societal perspective. Total costs will include the costs of administering POET or supportive treatment, as well as the use of other societal resources collected with the TIC-P, including health care resources, medication, social and school support services, and productivity losses due to absenteeism and presenteeism related to work. Total costs will be calculated for the full trial period by multiplying frequencies of resources by their respective unit costs. Regression models will be employed to estimate the differences in mean costs and mean effects between the groups over time. Incremental cost-effectiveness ratios (ICER) will be calculated as the difference in costs between the two interventions divided by the difference in effects (QALYs and response), for each type of analysis and each costing perspective. Sensitivity and scenario analysis will be conducted to explore the uncertainty around the estimates and different assumptions. The uncertainty will be plotted on cost effectiveness planes, and the probability of the intervention being cost effective will be calculated across different value levels a decision maker would be willing to pay and plotted on cost effectiveness acceptability curves.^51^

